##### Potential working mechanisms

Savoring will be measured with the 8-item savoring the moment subscale of the Savoring Beliefs Inventory (SBI; [12]). A 7-point scale from strongly agree (1) to strongly disagree (7) will be used to score items. Since four items are positively formulated and four are negatively formulated, sums score ranges from − 24 to + 24, with higher scores being indicative of a stronger savoring in the moment. Psychometric properties were found to be good [12, 37].

Self-reassuring will be measured with the 5-item reassuring self-subscale of the Forms of Criticism/Self-Attacking and Self-Reassuring Scale Short Form (FSCRS-SF; [36, 65]). Items will be scored on a 5-point scale ranging from not at all like me (0) to extremely like me (4). Sum scores will be calculated (0–20), with higher scores being indicative for a larger sense of self-reassurance. Psychometric properties were evaluated and found to be good [19, 55, 65].

Psychological flexibility will be measured with the 7-item Acceptance and Action Questionnaire-II (AAQ-II; [8]). Items will be scored on a 7-point scale ranging from never true (1) to always true (7). Sum scores will be calculated (7–49), with higher scores being indicative of larger psychological inflexibility levels. Psychometric properties were found to be good [8].

Positive coping skills will be measured with the subscales Acceptance, Positive refocusing, Positive reappraisal, and Putting into perspective of the Cognitive Emotion Regulation Questionnaire (CERQ; [35]). A 5-point scale ranging from (almost) never (1) to (almost) always (5). Sum scores will be calculated (4–20), with higher scores being indicative of a larger frequency of cognitive strategy use. Psychometric properties were found to be good [29, 60].

Mindfulness will be measured with the 15-item Mindfulness Attention Awareness Scale (MAAS; [11]). Items will be scored on a 6-point scale ranging from almost always (1) to almost never (6). Mean scores will be calculated, with higher scores being indicative of higher levels of mindfulness. Psychometric properties were evaluated and found to be good (e.g., [23]).

#### Characteristics of parents and children

Parental characteristics measured at screening include age and mental health support at the moment (i.e., whether parent self is in treatment for mental health issues) to determine eligibility. Parental characteristics measured at baseline (T0) include gender, age, education level, nationality, daily activities (e.g., employment), living situation (i.e., with/without partner, with one child with a NDD, with multiple children with a NDD, with one/more children with a NDD and one/more without a NDD), and marital status.

Characteristics about the child/children with a NDD include age, sex, diagnosis/diagnoses (i.e., the actual diagnosis, suspected of/formal diagnosis), language level (i.e., verbal, non-verbal, delay in language development), level of support required at school and in daily activities, sleeping issues (i.e., how well did the child sleep?), mental health support of the child(ren) (i.e., in the past or currently in treatment, use of medication). In case parents have multiple children with a NDD, they can respond for all children separately. To determine eligibility, the age and diagnosis are included in the screening, while the remaining characteristics are included in the baseline (T0) questionnaire.

#### Satisfaction with the intervention

Satisfaction with Adappt will be measured with the 8-item Client Satisfaction Questionnaire (CSQ-8; [4]). Satisfaction with the intervention will be measured in terms of quality of the intervention, fulfillment of needs and expectations, recommendation to other parents in a similar situation, helpfulness of the self-help app, satisfaction with the self-help app in general, and amount of support offered by the self-help app. Items will be scored on a 4-point scale, and a sum score (8–32) will be calculated with higher scores being indicative of a larger satisfaction with the self-help app. An excellent internal consistency was found by Kloos et al. [48].

Additional evaluative questions will be asked to get more insight in the evaluation of the app: (1) lessons learned from the self-help app, (2) themes that were perceived to be effective, (3) adherence as indicated by the number of days per week used, and minutes used per time, (4) functionalities (e.g., texts, videos, exercises, notifications/reminders, quotes, seeing progress, mindfulness exercises, traveling diary), and (5) content of the intervention (i.e., language used, amount of text, design, ease of use, and number of themes).

#### Logdata

Pseudonymized logdata will be collected automatically by the application. This logdata consists of information whether an exercise have been completed.

#### Dropout and retention

Dropouts will be asked to give feedback on the reason of withdrawal if they want to by asking “why did you decide to stop using the app?”. If a participant mentions problems with the app to be the reason, these will be communicated with the app developer and if fixed, the user will be contacted about this. Furthermore, to promote completion of the questionnaires, two reminders will be sent after an assessment point to non-completers.

### Data handling, management, and storage

The Dutch Personal Data Protection Act will be followed to handle data with confidentiality. Data management will be done following the data management plan (DMP) created for the study via the DMP-tool of the University of Twente, which complies to the policy of national funders and the EU. Personal data (i.e., e-mail addresses) will be collected for the purpose of sending questionnaires via the Qualtrics survey tool, which is ISO 270001 certified [59]. Personal data will be saved separately from the questionnaire data and can be linked to questionnaire data by means of a unique ID-code. Personal data can be accessed by the principal investigator for the purpose of informing participants about the screening for eligibility data and sending the questionnaire invitations. The list with IDs connected to personal data will be stored safely and locked with a password. The coded data will be safely stored for 15 years at the IGS Datalab of the University of Twente, which is ISO 27001 and NEN 7510-certified [75]. The first, second, third, and last author ([name]) of this paper will have access to the final pseudonymized dataset of this trial. Afterwards, pseudonymized data will be archived for long-term storage at Areda, the archiving service of the University of Twente. Participants get access to the self-help app via a personal activation code, this makes the log-data linkable with the study data (i.e., results from questionnaires).

### Statistical methods

#### Sample size calculation

The required sample size was computed with RMASS2 software for two-group longitudinal designs with attrition [39]. Given a required power of 80% and a two-sided significance level of 5%, 106 participating parents will need to be recruited in each arm to detect a linear trend effect over the first three time points (a group by linear time interaction from T0 to T2) resulting in at least a moderate effect size difference between the groups (Cohen’s *d* = 0.5) at 4 months after baseline. So, at least 212 parents must be included in this RCT.

This sample size estimation is based on the assumption that the repeated measurements follow a first-order autoregressive (AR1) variance–covariance structure (starting at *ρ* = 0.5 between repeated measurements) and an assumed attrition of 10% between both the baseline (T0) and post-intervention (T1) and between the post-intervention (T1) and 4 month follow-up (T2) measurements. Given the relatively low number of involved countries (five) in the trial and the self-help nature of the intervention, no relevant clustering between participants at the country level is anticipated in the sample size calculation.

#### Statistical analysis

Data of participants that provided incomplete baseline data will be removed from the dataset.

The study and data will be reported conform the Consolidated Standards of Reporting Trials (CONSORT) statement [62]. Data will be primarily analyzed based on intention-to-treat with linear mixed models (LMMs), since LMM fits the nested, repeated measures structure of this study, and can inherently deal with missing data on the outcome variable. The effectiveness of the app on all continuous primary and secondary outcomes, and potential working mechanisms between baseline (T0) to the first follow-up (T2) will be analyzed using LMMs with time, group and time-by-group interactions at fixed effects and with baseline scores as covariate [74].

Three additional within-group analyses will be performed by a LMM with time as the main effect to determine if intervention effects remained between T2 and T3 (in the intervention condition) and if there are improvements in the control condition after using the intervention at T3 (between T2 and T3). Between and within-group Cohen’s *d* effect sizes with 95% confidence intervals will calculated to estimate (potential) benefits of the intervention based on estimated marginal means and standard errors (from the LMMs). User satisfaction with the self-help app will be descriptively analyzed.

Single (one explanatory variable) and multiple (all five explanatory variables) mediation analysis will be performed to assess whether the explanatory variables mediated the effects of the intervention on the ability to adapt, mental well-being, perceived stress, depressive symptoms, and anxiety symptoms.

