### Waitlist control condition

Participants in the waitlist control group can start the self-help app after completing the first follow-up questionnaire, 4 months after baseline. The decision for a waitlist control has been made for ethical reasons, since these participants indicated a need for support by signing up for the intervention and we considered it not appropriate to withhold these participants from support for a longer period. With this design, the control group no longer serves as a control after the first follow-up questionnaire (4 months after baseline), since the participants may have then also started to use the self-help app.

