## Discussion

This protocol describes a study on the short- and long-term effectiveness of a self-help app based on positive psychology and mindfulness to support parents of children with a NDD in enhancing the sense of ability to adapt, and mental health. Furthermore, mediation analyses will be performed to find working mechanisms appearing to contribute to the effectiveness of the self-help app. Participants will be recruited in five countries, i.e., France, Germany, Israel, Switzerland, and The Netherlands; however, there are no limitations to the country participants live in, except for being able to speak one of the offered languages (French, German, Hebrew, or Dutch). The study will compare the intervention with a delayed waitlist control condition. The described study will contribute to knowledge on the effectiveness of support for parents of children with a NDD and give insight into working mechanisms that contribute to this effectiveness.

Several strengths are expected for the intervention and study. Firstly, this intervention has been developed in cocreation with the target group to meet the needs and preferences of the target group. Secondly, the exercises in the app are evidence based, increasing the chance of effectiveness of the intervention. Thirdly, the intervention involves a self-help app, having the advantage of being cost-effective, usable at any time the user prefers to, and easily scalable. Fourthly, this study adds to existing research by including mediation analysis to find working mechanisms. Fifthly, this is one of the first RCTs with a longer follow-up (6 months after the intervention).

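### The randomized comparison ends at T2, yet the Discussion claims long-term RCT effectiveness and the T3 analyses judge intervention effects from single-arm change

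*Protocol article*

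**What the plan says.** The protocol article confines randomized evidence to T0–T2 in three places.

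- Waitlist control condition: parents in this arm may start the app after the 4-month questionnaire, and "the control group no longer serves as a control after the first follow-up questionnaire".
- Sample size calculation: the powered contrast is "a group by linear time interaction from T0 to T2".
- Statistical analysis: the between-group mixed models run from baseline to T2.

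For the period after T2, Statistical analysis plans only within-group mixed models with time as the main effect. Their purpose is "to determine if intervention effects remained between T2 and T3 (in the intervention condition", and to see whether the waitlist arm improves between T2 and T3 once it has the app. Three such analyses are announced and two are described. Within-group Cohen's d with 95% confidence intervals is also planned.

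The Discussion opens with "This protocol describes a study on the short- and long-term effectiveness of a self-help app" and lists as a strength that "this is one of the first RCTs with a longer follow-up (6 months after the intervention". Neither sentence is qualified. The limitations that follow cover the expected majority of mothers, dropout and non-adherence. They do not mention the loss of the control arm.

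**The concern.** An intervention effect is a difference between arms. After T2 no untreated arm exists, so the effect at T3 cannot be estimated from what the trial collects. Stable scores in the intervention arm fit a kept effect, but also an effect that has shrunk because untreated parents would have caught up. A rise in the waitlist arm after T2 mixes the app with time, repeated measurement and selective loss of participants.

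At stake is the durability conclusion. The Introduction criticises earlier trials for rarely studying effects beyond 3 months, and the Discussion offers the longer follow-up as a strength of this one. A reader would take the T3 result as randomized evidence of lasting benefit. It would be a pre-post observation.

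**Working it through.** **1. Timing.** T2 is 4 months after baseline and the intervention lasts 1 month, so randomized evidence reaches 4 − 1 = 3 months after the intervention. The 6 months in the Discussion is T3 at 7 − 1 = 6. That fits the 7-month T3 in the Abstract, Study procedure and Table 2, but not the 6 months after baseline given in Study design. The Introduction glosses long-term as more than 3 months. T2 passes that mark if counted from baseline, but only reaches it if counted from the end of the intervention.

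**2. What the sample size covers.** Inputs from Sample size calculation: 80% power, two-sided 5%, d = 0.5 at T2, a "first-order autoregressive (AR1) variance–covariance structure" with ρ = 0.5, and 10% attrition in each of the two intervals. I take SD 1, contrast (−1, 0, 1), group differences (0, 0.25, 0.5) and retention 1, 0.90, 0.81.

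- Variance of the contrast = 1 + 1/0.81 − 2(0.5²)/√0.81 = 1.679
- n per arm = 2(1.960 + 0.842)² × 1.679 / 0.5² = 105.4, rounded up to 106

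The stated 106 per arm (212 in total) is reproduced. It powers the T0–T2 group contrast and nothing after it.

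**3. What a within-arm change can identify.** The effect at T3 equals the effect at T2 plus the T2–T3 change in the app arm minus the change that untreated parents would have had. The last term is unobserved. Illustration, starting from the planned 0.5 SD at T2:

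| Change, app arm | Change if untreated (unobserved) | Effect at T3 |
|---|---|---|
| 0 | 0 | 0.50 |
| 0 | +0.25 | 0.25 |
| −0.25 | −0.25 | 0.50 |

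The first two rows give the same data in the app arm but different effects. In the third, the arm declines and the effect is kept.

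**4. Precision of the within-arm test.** The document gives no attrition or correlation for T2–T3, so both are assumptions: attrition 0–30%, ρ 0.25–0.7, equal SDs, normal approximation.

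- Completers at T3 = 106 × 0.81 × (1 − attrition): 85.9, 77.3, 68.7 and 60.1 at 0, 10, 20 and 30%
- SE of the change = √(2(1 − ρ)/n)

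At 10% and ρ = 0.5:

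- SE = √(1/77.3) = 0.114 SD
- 95% CI half-width = 1.96 × 0.114 = 0.22 SD
- Smallest change detectable with 80% power = 2.80 × 0.114 = 0.32 SD

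Probability that a true within-arm loss of 0.25 SD (half the planned effect, if the untreated course is flat) is non-significant:

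| T2–T3 attrition | ρ = 0.25 | ρ = 0.5 | ρ = 0.7 |
|---|---|---|---|
| 0% | 0.527 | 0.361 | 0.151 |
| 10% | 0.566 | 0.406 | 0.190 |
| 20% | 0.606 | 0.455 | 0.237 |
| 30% | 0.647 | 0.509 | 0.294 |

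**5. If a formal maintained conclusion were wanted.** With an illustrative 0.25 SD margin, one-sided 0.025, 80% power and no true change, n = (1.960 + 0.842)² × 2(1 − ρ)/0.25². That is 126 completers in the arm at ρ = 0.5, 76 at ρ = 0.7 and 189 at ρ = 0.25, against roughly 60–86 expected.

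**The case against.** The protocol does not hide the design. It states that control is lost after T2, places the primary outcome at 4 months, restricts the between-group models to T0–T2 and labels the later analyses as within-group. No randomized inference at T3 is planned. The disputed claims are Discussion prose, and participants in this RCT are in fact followed to T3. All of that stands, and it is why the primary result is not in question. It does not cover the two unqualified Discussion sentences, or an analysis aim that names intervention effects where only one arm's change is observed.

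A reader might go further and infer that a non-significant T2–T3 change will be reported as effects having remained. The document does not say so. It states a purpose and a model but no decision rule, and it already plans within-group effect sizes with 95% confidence intervals. A margin may sit in the preregistered analysis plan, which is not shown. The probabilities above therefore describe how little a bare test would show; they are not the error rate of a rule in the plan.

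On dropout, mixed models accommodate missing outcomes and baseline comparisons of dropouts are planned. These help, but they do not supply a comparator.

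**Conclusion.** The point holds as a mismatch between claim and design. Randomized evidence stops at T2, about 3 months after the intervention. The long-term and 6-month wording, and the aim of finding whether effects persisted, rest on uncontrolled within-arm change. This follows from the text alone and needs no assumption.

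The numerical part is supporting only. A 0.25 SD loss would go undetected in about 15–65% of trials across the assumed attrition and correlation, and in about 41% at 10% attrition and ρ = 0.5. It would be wrong to say that the plan equates non-significance with maintenance, or that it is defective for lacking a margin. The primary endpoint, sample size and main model are unaffected. The mismatch between three analyses announced and two described is a minor slip and carries no weight here.

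**What to change.** - Discussion: limit effectiveness claims to T0–T2, say that follow-up after T2 is uncontrolled, and add this to the limitations.
- Statistical analysis: rename the later analyses as within-arm change from T2 to T3, uncontrolled and descriptive, in both arms. Interpret them from the 95% confidence intervals already planned, not from non-significance.
- Set a margin in advance only if a maintained conclusion is wanted. As shown above, the expected number of completers may be too small to support one, and even a precise result would concern the arm's scores and not the effect of the app.
- Reconcile the number of within-group analyses announced with those described, and the 6- and 7-month timings of T3.

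The cost is wording, with no new data or participants. The real price is a less favourable durability claim.

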### Ethics

Before the start of the study, a non-WMO declaration of the Medical Ethical Committee (METC) Oost Nederland and ethical approval of the ethics committee of the University of Twente (approved at January 10, 2024) were obtained. Amendments of the protocol will be re-evaluated by the METC Oost Nederland, the ethical board of the University of Twente, and communicated with the trial register. The study will be conducted in accordance with the principles of the Declaration of Helsinki (64th WMA General Assembly, Fortaleza, Brazil, October 2013) and with the Good Clinical Practice guidelines. Individual clinical trial participant-level data (IPD) will not be shared.

### Risks and audit

Participants will be informed on the study and give informed consent before the start of the trial. After the screening, participants with major mental health issues will be advised to go to their general practitioner. Based on previous studies of comparable applications for other target groups [48, 74], no risks of participation are foreseen. As this study is declared to be non-medical (non-WMO), audits and a data monitoring committee are not planned.

## Results

Data collection is expected to be completed by the end of 2025.

### Publication policy

Results (on group level) of this study will be published in at least one international peer-reviewed journal. Results will be reported in a final report for the subsiding party (the European Union). No specific arrangements are made between the sponsor and the investigator concerning the public disclosure and publication of the research data. Participants can receive a summary of results (on group level) of the study upon request.

## Discussion

This protocol describes a study on the short- and long-term effectiveness of a self-help app based on positive psychology and mindfulness to support parents of children with a NDD in enhancing the sense of ability to adapt, and mental health. Furthermore, mediation analyses will be performed to find working mechanisms appearing to contribute to the effectiveness of the self-help app. Participants will be recruited in five countries, i.e., France, Germany, Israel, Switzerland, and The Netherlands; however, there are no limitations to the country participants live in, except for being able to speak one of the offered languages (French, German, Hebrew, or Dutch). The study will compare the intervention with a delayed waitlist control condition. The described study will contribute to knowledge on the effectiveness of support for parents of children with a NDD and give insight into working mechanisms that contribute to this effectiveness.

Several strengths are expected for the intervention and study. Firstly, this intervention has been developed in cocreation with the target group to meet the needs and preferences of the target group. Secondly, the exercises in the app are evidence based, increasing the chance of effectiveness of the intervention. Thirdly, the intervention involves a self-help app, having the advantage of being cost-effective, usable at any time the user prefers to, and easily scalable. Fourthly, this study adds to existing research by including mediation analysis to find working mechanisms. Fifthly, this is one of the first RCTs with a longer follow-up (6 months after the intervention).

Several limitations are also expected in advance. Firstly, it is expected that majority of participants will be mothers, limiting the generalizability of conclusions to fathers. This is expected since the recruitment of participants for the development phase has shown that recruiting fathers is much harder than recruiting mothers. This is also in line with research on the effectiveness of positive psychology interventions across different populations, since the bibliometric analysis of Hendriks et al. [41] showed that almost three-quarters of participants was female in 180 studies. Furthermore, mothers are perceived to be the primary caregiver of children with a NDD [2, 50]. Secondly, study dropout and intervention non-adherence can result in bias [28]. Post hoc analysis will be performed to compare baseline characteristics of study dropouts at post-intervention, 3-month follow-up, and 6-month follow-up.

